### Blinding

On screening, participants will be informed that two possibly effective programmes will be investigated. To reduce expectation bias, it will not be made known to participants whether the wilderness programme is hypothesised to be better than a hotel stay (single blinded). Statistical analysis will be performed by a statistician who is blind to programme allocation.

### Data management and confidentiality

Study data of each participant will be handled in a case report form (CRF). Self-reported demographic data, medical data (cancer diagnosis, cancer treatment, medical history, etc), and other relevant intervention-related data (preference, expectations, effectiveness, etc) will also be documented in the CRF. Participants are allowed to continue all their medication, therapies and/or dietary and lifestyle measures during the study. Any changes in medication, therapies, dietary and lifestyle measures over time will be documented in the CRF. CRF data will be anonymised for analysis by assigning each participant an unidentifiable three-digit screening number at the time of enrolment and additional three-digit study number on randomisation. The CRF, SPSS dataset and other participant-related documentation will be stored on a secure server at Mid Sweden University or Agder University and can only be accessed with a password by research team members who are authorised. To guarantee data quality, independent checks during data collection and data entry will be performed by another researcher than the one collecting or entering the data in the database. A data monitoring committee will not be established because of the nature of the study (health-promotion intervention with low risk). The collected data will be saved for at least ten years after the end of the study.

### Data analysis

χ^2^ statistics, independent samples t-tests and analysis of variance will be used to calculate group differences in sociodemographic variables and cancer characteristics at baseline. The alpha level will be set to 0.05. The primary analysis will investigate changes in the total scores of the PWS and NRS over time from baseline to 1- year follow-up in the intervention group compared with the control group. Missing data will be imputed by means of multiple imputations or by using full-information maximum likelihood estimation.^41^ The analysis of the primary outcome will be based on a linear mixed-effects model and will be fitted to test intervention effects up to 1 year. Adjustments will be made for age, gender, age at cancer diagnoses and study site. Time, intervention arm, interaction between time and intervention arm, age, gender, age at cancer diagnoses and study site are included as fixed effects, and the participant is included as random effect in the model. Statistical analyses will be on the intention-to-treat principle (all participants who are randomised in the study). As sensitivity analyses, the per-protocol data set will be analysed including only participants who have participated for at least 1 day in the wilderness or hotel stay. Secondary outcomes will also be analysed using linear mixed-effects models.

Categorical data will be presented as frequencies and percentages. For continuous data, the number, mean, SD, median, IQR, minimum and maximum will be calculated. A two-sided p<0.05 will be considered statistically significant.

Safety analyses will be performed on the safety analysis set and include all individuals who had participated in one of the programme interventions for at least 1 day. RR with 95% CI will be calculated to indicate the risk of having an AE adjusted to days of exposure to programme interventions. Pearson’s χ^2^ test will be used to calculate differences in AEs severity between the two study arms. A detailed description of the planned statistical analyses will be provided in the statistical analysis plan, which will be finalised prior to database closure and data analysis. All statistical analyses will be performed by using Stata V.18.0.

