### Intervention group: wilderness programme

The development of the WAYA programme affected by cancer has previously been published.^24^ The WAYA programme aims to increase physical activity, self-confidence, self-efficacy and self-care, to support personal growth and building meaningful relationships, and to provide an enjoyable and safe stay in nature. Nature in the WAYA programme has both a contextual and an active role in support of the health and well-being of AYAs affected by cancer, wherein their health is regarded to be intrinsically interwoven in a bidirectional fashion with the health and well-being of nature.^29^ Participants are given the opportunity to experience a diversity of natural landscapes, and specific nature characteristics are actively incorporated in programme activities. Activities in the programme include hiking, sea-kayaking, backpacking, rock climbing and camping. The programme also includes (nature) reflective practices such as mindfulness, meditation and forest bathing.^24^ Outdoor skills taught include mapping/compass/orienting, trail cooking, safety training, equipment planning, foraging, fishing, bush-craft skills and leaving no trace. The wilderness programme consists of three intervention parts: (1) An 8-day intervention that includes 2 days for travelling and physical testing and a 6-day wilderness expedition; (2) A 3-month in-between period where participants are contacted once every month online to coach them to engage in their own outdoor activities and (3) A 4-day intervention including a 2-day base camp programme. Both the expedition and basecamp programme will take place in natural settings around the High Coast of Sweden or in Southern Norway. The group size will be 10–12 participants, and the facilitator–participant ratio will be 3:10. The 6-day wilderness expedition will be logistically supported by a team of 5–7 volunteers.

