### Control group: hotel stay

The hotel stay will be for 8 days at a Spa Hotel in Sweden or Norway, including 2 days for travelling and physical testing and a 6-day hotel stay, followed by a second 4-day stay at the same hotel (including two travel days) 3 months later. Similar to the wilderness intervention, during the 3-month in-between period, participants will be contacted once every month to ask how they are doing. The content of the hotel stay includes the following activities: Spa facilities, museum visits, watching television/movies, playing games/gaming, shopping and fine dining. Participants will engage in organised group activities, but this does not include any nature-based activities. The group size is 10–12 participants, and the facilitator–participant ratio will be 3:10.

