### Sample size

The current study aims to recruit a total of 150 participants who will be randomised into two groups (n=75 per group). The power calculation is based on a two-group linear mixed-effects model for repeated measures data with attrition^38^ and provides 80% power to detect a medium-sized between-group difference (SMD=0.60). In the sample size estimation, we account for an attrition rate of 34.5% before the start of the intervention as reported in the previous pilot study^25^ and a low attrition rate (10%) during the intervention. The power calculation is based on a model with four repeated measurement points, a first-order autoregressive correlation structure, an initial repeated measures correlation of 0.60 (with decreasing magnitude of the repeated measures correlations with increasing distance between time points), an alpha level of .05, and a group allocation of 1:1.

The effect size estimates for the primary outcomes are based on a meta-analytical estimate^32^ of a standardised between-group difference of 0.69 (Hedges’ g) for interventions to enhance eudaemonic psychological well-being, and findings from a pilot study indicating a significant between-group difference in NRS between the wilderness programme and hotel stay (Cohen’s d=0.63).^25^

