One of the expected challenges of this study is to recruit the needed number of participants in the study within the set time frame. We previously published that the eligibility (87.3%) and enrolment rate (95.2%) of participants in the WAYA-1 study were high.^25^ To randomise 150 eligible individuals into the WAYA-2 study, we, therefore, need to recruit at least 180 AYAs affected by cancer to register their interest to participate in the WAYA-2 study. In our previous pilot study, we only recruited among members of Swedish cancer organisations Ung Cancer and the Childhood Cancer Fund, and the recruitment rate was low (3.6%).^25^ However, the pilot study was performed during the COVID-19 pandemic where recommendations with respect to travel restrictions were in place. It is, therefore, expected a higher recruitment rate in the WAYA-2 study. Furthermore, we will now also recruit participants in Norway and additional recruitment strategies will be developed with the support of healthcare professionals and brochures in waiting rooms of oncology departments of hospitals in Norway and Sweden.

Another potential challenge of the WAYA-2 study is the inclusion of a heterogeneous study population (all cancer diagnosis and all cancer treatment stages) with a wide age range (16–39 years). Programme activities and study outcomes may be affected by participants being at very different stages of their cancer trajectory and/or lives. The inclusion of participants with a large span was investigated in detail in the previous pilot study and results have been published.^24^ It appeared that the wide age range and different stages in the cancer process were perceived to be an advantage (rather than a disadvantage) since it positively influenced group bonding and learning process, according to facilitators and participants.

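### The 5% error rate and 80% power hold only if outcomes are essentially uncorrelated within the treatment groups of 10–12, because the primary model and sample size allow for no group effect

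*Protocol article*

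**What the plan says.** The protocol article describes individual randomisation to two parallel arms (Study guidance and design). Delivery is in groups. For the wilderness arm, "The group size will be 10–12 participants"; for the hotel arm, "The group size is 10–12 participants". Both have three facilitators per ten participants. The hotel comparison is meant to control for attention and group support, among other things, so group support is named as a factor that may itself be effective.

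Data analysis lists the fixed effects of the primary model: time, arm, time by arm, age, gender, age at diagnosis and study site. It then states that "the participant is included as random effect in the model". No term for the expedition or hotel group appears. The threshold for the tests is also fixed: "A two-sided p<0.05 will be considered statistically significant".

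Sample size lists 80% power at a standardised difference of 0.60, attrition of 34.5% before and 10% during the intervention, four time points, a first-order autoregressive correlation starting at 0.60, and "an alpha level of .05, and a group allocation of 1:1". It gives no ICC, design effect or number of groups.

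**The concern.** People who spend a week together under the same facilitators, with the same weather and the same route or hotel, may end up more alike than people in different groups. Individual randomisation makes the arms comparable at baseline, but it does not prevent correlation that shared treatment creates afterwards. Study site as a fixed effect separates the countries, not the groups within a country.

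If such correlation exists, a model with only a participant random effect understates the standard error of the arm contrast. Both confirmatory outcomes, the psychological well-being and nature relatedness scales, use this model, so both would be tested at more than the nominal 5%. Once the standard error is corrected, power would fall below the stated 80% unless the chosen contrast has power to spare.

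**Working it through.** **Reproducing the planned number.** Inputs are from Sample size and Data analysis: difference 0.60 SD, two-sided alpha 0.05, power 80%.

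- Per arm, independent participants: 2 × (1.960 + 0.842)² / 0.60² = 43.6, so 44 (power 80.4%).
- Attrition during the intervention: 44 / 0.90 = 48.9, so 49.
- Attrition before the intervention: 49 / 0.655 = 74.8, so 75 per arm, 150 in total.

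This matches the plan exactly. For a single-time-point comparison there is no slack.

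**Number of groups.** The article does not state it. About 49 starters per arm in groups of 10–12 make 49/12 = 4.1 to 49/10 = 4.9, so about 4–5 groups per arm.

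**Effect of clustering, single time point.** The ICC is an assumption. With group size m = 10–12 and n = 44 analysed per arm:

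- Design effect: DE = 1 + (m − 1) × ICC.
- Type I error if clustering is ignored: 2 × [1 − Φ(1.960/√DE)].
- Power with a valid standard error: Φ(0.60/√(2·DE/44) − 1.960).
- Power with group-level degrees of freedom: noncentral t, df = 2 × 44/m − 2.

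| Assumed ICC | DE | Type I error if ignored | Power, valid SE (z) | Power, group-level df |
|---|---|---|---|---|
| 0 | 1.00 | 5% | 80.4% | 63–67% |
| 0.01 | 1.09–1.11 | 6.0–6.3% | 76–77% | 59–64% |
| 0.02 | 1.18–1.22 | 7.1–7.6% | 72–74% | 55–60% |
| 0.05 | 1.45–1.55 | 10.4–11.5% | 62–65% | 46–52% |

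The last column is a conservative bound, since Kenward-Roger or Satterthwaite df can be larger.

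If the participant-only model is kept, the rejection rate at 0.60 falls only to about 75–79% over ICC 0.01–0.05. Under the model as planned, the main harm is false positives; the larger loss of power appears once the standard error is corrected.

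**Dependence on the contrast.** Sample size does not say which contrast is powered. For the mean of the three follow-ups under the stated autoregressive correlation, the variance of one participant's mean is (3 + 2 × (0.60 + 0.60 + 0.36))/9 = 0.68. With a group correlation that is constant over time, the standard error is √(2 × (0.68 + (m − 1) × ICC)/44). Power (z) is 93% at ICC 0, 84–86% at 0.02 and 72–75% at 0.05.

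**Which group term works.** The footnote to Table 1 places the baseline questionnaires 2–3 weeks before the first intervention, so group correlation can arise only after baseline. Take 4 groups of 11 per arm, complete data, participant plus residual variance 1, constant correlation 0.60 between occasions, and a group variance of 0.05 that starts after baseline. For change from baseline to 1 year:

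- Participant-only model: SE = √(2 × 2 × (1 − 0.60)/44) = 0.191.
- With a time-constant group intercept added: still 0.191, because the intercept cancels from change.
- True SE: √(0.0364 + 2 × 0.05/4) = 0.248. A group effect that starts after baseline recovers this value.

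The ratio is 0.248/0.191 = 1.30. Ignoring clustering would give a type I error of 2 × [1 − Φ(1.960/1.30)], about 13%, for this contrast, so the single-time-point figures are not an upper bound.

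**The case against.** The strongest objection is that the size of the problem rests on an ICC that the article does not give. That stands. A reader might infer that the standard errors are certainly too small and that 80% power is certainly missed. The document supports neither. What it supports is conditional: any positive ICC makes the stated model anticonservative, by an unknown amount.

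The contrast matters too. A comparison averaged over follow-ups would still exceed 80% (z) at an assumed ICC of 0.02, though not at 0.05. The effects cited for the two outcomes, 0.69 and 0.63, exceed 0.60 and give 90% and 84% power without clustering in the single-time-point comparison. At ICC 0.05 these fall to 74–77% and 66–69%. Higher power does not correct an understated standard error.

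Two further inferences go beyond the text. The Discussion might be read as reporting that group bonding affects outcomes. Its subject is the wide age range and the different cancer stages, of which it says that "it positively influenced group bonding and learning process"; no effect of bonding on either primary scale is reported. Nor does the article say that the same people meet again at the second stay; the hotel section says only that the hotel is the same.

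The article defers detail to a statistical analysis plan, which may exist but is not at hand. Ordinary detail can be left there, but the article itself states the random-effects structure, and a plan that followed it would carry the problem forward.

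**Conclusion.** The point holds in conditional form. The protocol article fixes a participant-only random effect for a treatment delivered in groups, and its sample size reproduces with no clustering allowance. The 5% error rate and 80% power therefore require an ICC of essentially zero, which is hard to presume when the article itself treats group support as a possible active factor.

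Over an assumed ICC of 0.01–0.05, the single-time-point error rate is about 6–12% if clustering is ignored, and power with a valid standard error is about 77% down to 62%, lower with group-level df. These figures rest on 44 analysed per arm, groups of 10–12 and a difference of 0.60. They change with the contrast, in either direction. The document does not show that power fails at every plausible ICC.

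**What to change.** In the primary and secondary mixed models, add a programme-group random effect that acts after baseline, as group-by-post or group-by-time, in both arms. A time-constant group intercept is not enough. Use Kenward-Roger or Satterthwaite degrees of freedom.

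The intention-to-treat set includes everyone randomised, and 34.5% are expected to leave before the intervention. Treat non-starters who were never in a group as unclustered, with a sensitivity analysis that places them in their planned group where one was recorded.

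Name the powered contrast and restate its power over an assumed ICC range, for example 0.01–0.05, without changing n. Data analysis says the statistical analysis plan will be finalised before database closure, so the change can be prespecified there and recorded in the trial register, as Protocol amendments provides.

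The cost is one model component, wider intervals and a less favourable power figure. The only data needed are each participant's group, which the trial should know. The group variance will be imprecisely estimated from about 4–5 groups per arm, which is why the small-sample df are needed.

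### About a third of those randomised are expected never to start, and the named sensitivity analysis removes them, so unless they return questionnaires it cannot show whether their loss biases the result

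*Protocol article*

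**What the plan says.** All of this is in the protocol article; the statistical analysis plan to which it defers is not shown.

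- **Size and expected loss (Sample size).** The target is 150 randomised, 75 per arm. The authors write that "we account for an attrition rate of 34.5% before the start of the intervention as reported in the previous pilot study", and add "a low attrition rate (10%) during the intervention".
- **Recruitment (Discussion).** "To randomise 150 eligible individuals into the WAYA-2 study, we, therefore, need to recruit at least 180 AYAs affected by cancer". This rests on the pilot's eligibility (87.3%) and enrolment (95.2%) rates.
- **Primary analysis (Data analysis).** Intention-to-treat on everyone randomised, with a linear mixed model containing a time-by-arm interaction. On missing values: "Missing data will be imputed by means of multiple imputations or by using full-information maximum likelihood estimation".
- **Sensitivity analysis (Data analysis).** "As sensitivity analyses, the per-protocol data set will be analysed including only participants who have participated for at least 1 day". The safety analysis set uses the same threshold of one day.
- **Timing (Table 1 and its footnote).** Preference and expectations are recorded at screening, before randomisation. Baseline questionnaires are completed 2–3 weeks before the first stay, and later ones outside the stays.

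**The concern.** A sensitivity analysis should show whether the conclusion survives a different assumption about what could not be observed. Here the largest unobserved group is expected to be people who were randomised and then never took part. The primary analysis handles them by assuming that, given the data in the model, they would have fared like those observed in their arm. The named sensitivity analysis removes them. It varies who is counted, not what is assumed about those who are missing.

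The loss could well be selective. Blinding hides only which programme is hypothesised to be better, so participants know their allocation before they decide whether to travel. If the two results agree, a reader may take that as evidence of robustness, and an effect among starters could pass for the effect in everyone randomised.

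**Working it through.** **1. Where the 34.5% falls.**

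Inputs from Sample size and Data analysis: SMD 0.60, 80% power, two-sided alpha 0.05, losses of 34.5% and 10%.

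- Per arm before losses: 2 × ((1.96 + 0.842)/0.60)² = 43.6, so 44.
- With both losses: 44/((1 − 0.345)(1 − 0.10)) = 44/0.5895 = 74.6, so 75 per arm and 150 in total. This reproduces the plan's figure.
- With the 10% loss only: 44/0.90 = 48.9, so 49 per arm.
- Variants that also count the 34.5% within the randomised total come close: 154 with a t-based calculation, and 146 with a repeated-measures formula (AR(1), correlation 0.60, four visits, final-visit contrast).

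The Discussion agrees. 180 × 0.873 × 0.952 = 149.6, so eligibility and enrolment alone take 180 registrants to 150 randomised. No room is left for a 34.5% loss before randomisation.

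**2. What this implies for missing data.**

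| Group | Arithmetic | Result |
|---|---|---|
| Never start | 150 × 0.345 | about 52 |
| Start | 150 × 0.655 | about 98 |
| Observed at the end | 150 × 0.655 × 0.90 | about 88 (59%) |

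If non-starters return nothing, they make up 0.345/(1 − 0.5895) = 0.345/0.4105 = 84% of the missing 1-year outcomes. The at-least-1-day set removes all of them. It keeps those who leave later, under the same missing-at-random assumption.

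**3. Whether the two analyses can disagree.**

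This was checked by simulating 600 trials of 75 per arm, with four visits and AR(1) correlation 0.60. In each arm 34.5% never start and give no post-baseline data, and 10% of starters miss the last visit. Assumed, not in the documents: the effect is 0.60 SD in wilderness starters and 0 in non-starters. The estimate is the arm difference in change from baseline to the last visit.

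| Baseline of non-starters | True effect, all randomised | Likelihood-based ITT | At least 1 day |
|---|---|---|---|
| Observed | 0.39 | 0.61 | 0.60 |
| Not observed | 0.39 | 0.59 | 0.59 |

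Without a baseline from non-starters the two analyses are identical in every trial. With a baseline they differ within single trials (SD of the difference 0.09), but this is sampling noise around nearly the same wrong value.

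**4. What an analysis that varies the assumption would show.**

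Let wilderness non-starters be d SD lower than missing-at-random predicts, with hotel non-starters as predicted. The effect in all randomised is 0.60 − 0.345d:

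- d = 0.2: 0.53
- d = 0.4: 0.46
- d = 0.6: 0.39, the same as 0.60 × 0.655

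An equal shift in both arms, with equal non-start, would cancel. What matters is a difference between the arms.

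**The case against.** **Detail is left to the statistical analysis plan.** An article need not list auxiliary variables or analyses under missing-not-at-random, and the unseen plan may contain both. This stands as a limit: the per-protocol analysis is the only one named here, not necessarily the only one planned. The point does not rest on missing detail, because the article itself states which analysis carries the sensitivity label.

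**The article never says that the per-protocol set tests the missing-data assumption.** True. Comparing intention-to-treat with per-protocol is conventional and speaks to participation. But with this pattern of loss and no follow-up of non-starters, it would say little about that either.

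**Non-starters may still be followed up.** This is the strongest objection. The 34.5% is a sample-size allowance, the primary outcomes are self-completed outside the stays, and nothing says that mailings stop. A reader might infer that the plan drops non-starters from follow-up, but the text does not support that. If many respond, the two analyses can differ, and the subset becomes a real contrast by adherence. It would still not vary the missing-data assumption.

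**Preference-driven loss.** A reader might go further and conclude that arm preference biases the estimate by a known amount, or that the preference data go unused. Neither is supported. The documents give no retention by preference. A constant difference in level between preference groups would largely drop out of the time-by-arm contrast. The fixed effects are listed, but the imputation model is not. Excluding people unwilling to be randomised may also reduce such loss.

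**Conclusion.** The point holds in conditional form. The sample-size arithmetic and the recruitment figures together place the 34.5% after randomisation, about 52 of 150. The analysis named as the sensitivity analysis removes those people and keeps the missing-at-random assumption. If they give no post-baseline data, it will nearly match the primary result even when that assumption is badly wrong.

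The gap of 0.60 against 0.39 is an illustration, not a forecast. It assumes no benefit in wilderness non-starters, 34.5% non-start in that arm, hotel non-starters as predicted, and no follow-up data from non-starters. The documents do not show that the loss will be selective. They show that the named analysis could not reveal it. Because the protocol itself budgets for so large a loss before the start, this should be put right before the analysis plan is finalised.

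**What to change.** 1. For both primary outcomes, make the sensitivity analysis a multiple imputation on all randomised that departs from missing-at-random: delta-adjusted over a stated range, with the shift allowed to differ by arm, and/or reference-based (jump-to-control).
2. Include screening preference and expectations, which are already collected, as auxiliary variables in the imputation.
3. State that the self-completed T1–T3 questionnaires go to everyone randomised, including those who never start.
4. Keep the at-least-1-day analysis, but label it supplementary.

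The cost is some follow-up mailings and a little more analysis. The sensitivity analysis may also give a smaller effect estimate than the primary one. The article says that the analysis plan will be finalised before database closure and that protocol changes are documented in the trial register, so both routes are available. The sample size does not need to change for this point.

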### Outcomes

The selection of outcomes is driven by the aims of the WAYA programme and recently published qualitative study results of the WAYA programme.^26^ The aims of the WAYA programme and underlying process to support self-realisation via nature connectedness are hypothesised to contribute to a chain of actions that impacts the six domains of Positive Health.^25^ The WAYA programme is a complex intervention and may potentially impact multiple factors. Therefore, in line with guidance and instructions for RCTs on complex interventions, more than one primary outcome is chosen in relation to the research questions.^30^

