#### Primary outcomes (confirmatory)

Changes in psychological well-being of AYAs affected by cancer over time, measured by the Psychological Well-being Scale (PWS).^31^ This scale consists of six domains: self-acceptance, positive relations with others, autonomy, environmental mastery, purpose in life and personal growth. Together, these dimensions can contribute to the assessment of a person’s level of positive functioning and well-being. This instrument is translated and validated in the Swedish context.

Rationale: Significant and relevant changes in the PWS have been demonstrated for complex interventions including mindfulness-based programmes.^32^ The PWS was not included as an outcome measure in our previous pilot study,^1^ but based on the findings from the qualitative study of the WAYA programme, we have selected PWS as a primary outcome measure.^26^ For the qualitative analysis of the pilot study, participants in the wilderness programme were interviewed at 3 months after start of the programme to explore the impact of the programme on their health and well-being. The themes that arose through the inductive content analysis related to self-confidence, self-acceptance, meaningful relationships and personal growth. These themes are also reflected within the domains of the PWS providing additional richness to the data.^31^

Changes in nature connectedness of AYAs affected by cancer over time, measured via the Nature Relatedness Scale (NRS).^33^ The NRS is a 21-item scale that measures the ‘affective, cognitive and physical relationship individuals’ have with the natural world. For the purpose of the previous pilot study,^25^ the NRS was translated and validated in the Swedish language (results not published).

Rationale: In line with guidance and instructions for RCTs on complex interventions,^30^ nature connectedness is hypothesised to be the underlying mechanism (intermediate outcome) along the theorised impact path towards eudaemonic (psychological) well-being. A significant increase in NRS has previously been demonstrated in childhood and AYA cancer survivors after participation in the WAYA programme compared with the hotel stay.^25^

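### Two confirmatory primary outcomes (PWS and NRS) share one unadjusted two-sided 0.05 threshold, with no testing order, alpha split or both-must-succeed rule

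*Protocol article*

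**What the plan says.** In the protocol article, the Outcomes section says that "more than one primary outcome is chosen in relation to the research questions", citing guidance on complex interventions. PWS and NRS are then listed under the heading "Primary outcomes (confirmatory", while the secondary outcomes are headed exploratory. The label is therefore a deliberate inferential claim. In the rationale for NRS, "nature connectedness is hypothesised to be the underlying mechanism (intermediate outcome" on the path to psychological well-being. The Research questions section asks about the two outcomes separately.

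Under Data analysis, "The primary analysis will investigate changes in the total scores of the PWS and NRS over time". The same section says "The alpha level will be set to 0.05" and later "A two-sided p<0.05 will be considered statistically significant". No other threshold appears.

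Under Sample size, the calculation "provides 80% power to detect a medium-sized between-group difference (SMD=0.60" and uses "an alpha level of .05, and a group allocation of 1:1". Separate source effects are cited: 0.69 for eudaemonic well-being and 0.63 for NRS. The article gives no alpha split, no order of testing and no rule on whether one or both outcomes must be significant. A fuller account of the analyses is left to a statistical analysis plan, to be finalised before database closure.

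**The concern.** Calling an outcome confirmatory implies that the error rate of the claim is controlled. With two such outcomes, each judged at 0.05, that control depends on a decision rule, and the article gives none. Three rules fit the text, and they behave differently:

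- **Either outcome suffices:** the false-positive rate exceeds 5%.
- **Both are required:** alpha is controlled, but joint power is below 80%.
- **A fixed order:** alpha is controlled, and the stated power holds for the first outcome only.

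A split result is realistic. NRS is the hypothesised mechanism, the pilot reported a significant NRS difference, and the hotel programme excludes nature-based activities. If NRS is significant and PWS is not, the article does not say whether effectiveness has been confirmed. That should not be settled after the results are known.

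**Working it through.** **Inputs.** From Sample size: SMD 0.60, 80% power, alpha 0.05, 75 per arm, attrition of 34.5% before and 10% during the intervention. From Data analysis: two-sided p<0.05 for both outcomes. Assumed, because not stated: the correlation r between the two test statistics, varied from 0 to 0.9.

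**1. Reproducing the stated sample size.**
- n = 2 × ((1.960 + 0.842)/0.60)² = 43.6, so 44 evaluable per arm.
- 44/(0.655 × 0.90) = 74.6, so 75 per arm, as stated.
- In reverse, 75 × 0.655 × 0.90 = 44.2 evaluable. The noncentrality is 0.60 × √(44.2/2) = 2.821, and power = Φ(2.821 − 1.960) = 80.5% (79.7% with the t distribution).

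The figure therefore reproduces for one outcome at unsplit alpha 0.05. This is a reconstruction. The protocol names a mixed model with four measurements and AR(1) correlation 0.60 but does not give the time contrast. Trying several contrasts and attrition patterns at alpha 0.05 with 10% attrition gave about 27 to 83 per arm before the 34.5% inflation, so that route does not settle the matter.

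**2. Family-wise error if either outcome counts.**
For independent tests: 1 − 0.95² = 9.75%. For correlated tests: 1 − P(|Z₁|<1.96 and |Z₂|<1.96) under a bivariate normal.

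| r (assumed) | Family-wise error |
|---|---|
| 0 | 9.75% |
| 0.3 | 9.51% |
| 0.5 | 9.07% |
| 0.7 | 8.35% |
| 0.9 | 7.04% |

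**3. Power under each possible rule, N=150, SMD 0.60** (normal approximation, t-based values where given).
- *Fixed sequence:* PWS keeps 80.5%. A confirmatory NRS result needs both outcomes significant: 0.8054² = 64.9% at r=0 and 72.0% at r=0.7, if both effects are 0.60.
- *Both required:* the same joint power, 64.9% to 72.0%.
- *Alpha 0.025 per outcome:* Φ(2.821 − 2.241) = 71.9% (70.5% with t). This is also approximately the worst case for Holm, when the other outcome has no effect.
- *Holm, both effects 0.60:* at r=0, power per outcome = π(0.025) + [π(0.05) − π(0.025)] × π(0.025), where π(a) is single-test power at level a. This gives 0.7189 + 0.0865 × 0.7189 = 78.1% (about 77% with t). At r=0.7 it is 76.6% (about 75% with t). The range is about 75–78%.

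**4. Sample size to restore 80% at alpha 0.025.** n = 2 × ((2.241 + 0.842)/0.60)² = 52.8, so 53 evaluable. 53/(0.655 × 0.90) = 89.9, so 90 per arm, about 180 in total.

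**The case against.** The strongest reply is that this belongs in the statistical analysis plan, which is not shown. A fixed sequence or a both-must-succeed rule could be added there without contradicting the 0.05 in the protocol. That much stands, and the eventual plan may contain such a rule. It is not a full answer, because the protocol already applies the confirmatory label, the single threshold and the power claim without qualification. A later alpha split would conflict with the first 0.05 statement and reduce the stated power. A both-must-succeed rule would leave the 80% untrue of the trial's success criterion.

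It can also be said that the inflation presupposes a rule the article never states. This is correct. A reader might infer that a win on NRS alone would count as proof of effectiveness, but the text does not say so. It calls NRS intermediate, and the Discussion frames the aim around psychological well-being. The error rates above are therefore conditional on an either-outcome reading.

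The 9.75% is the independence value. The outcomes are hypothesised to lie on one causal path, so positive correlation is plausible and the rate may be lower.

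The source effects of 0.69 and 0.63 exceed 0.60. At alpha 0.025 with 44 per arm they would give about 83% and 75% power. The plan's own target is 0.60, however, so power should be restated there.

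**Conclusion.** The point holds as a stated threshold that does not match the confirmatory claim. If either outcome may confirm the trial, the family-wise error is 8.35% to 9.75% for correlations from 0.7 to 0, and still 7.04% at 0.9. The stated 80% power is right for one outcome at full alpha, on the two-means reconstruction. It does not describe a design with split alpha or one requiring both outcomes.

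Three stronger readings are not supported:

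- **Six tests.** A reader might count two outcomes at three post-baseline visits and infer a much larger error. The protocol describes a mixed model with a time-by-arm interaction and does not say that each visit will be judged separately at 0.05.
- **Power of 70% under Holm in general.** That is the Bonferroni figure and Holm's worst case. With both effects at 0.60, Holm gives about 75–78%.
- **The 1-year visit as the only acceptable primary contrast.** It is one reasonable option. The plan describes a longitudinal comparison up to 1 year, and the multiplicity point does not depend on the visit chosen.

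**What to change.** Before any data are analysed, amend the protocol by the route in Protocol amendments, and carry the same wording into the statistical analysis plan.

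**Preferred: fixed sequence.** Test PWS first at two-sided 0.05. Treat NRS as confirmatory, also at two-sided 0.05, only if PWS is significant. Otherwise report NRS as supportive. This matches the article's emphasis on well-being and keeps N=150, alpha 0.05 and the stated power for PWS. It takes about one paragraph. The cost is that NRS alone cannot be claimed as confirmatory.

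**Alternative: Holm across PWS and NRS.** Either outcome can then be claimed alone with family-wise error held at 0.05. Restate power per outcome at SMD 0.60 as about 70% in the worst case (alpha 0.025, no effect on the other outcome) and about 75–78% if both effects are 0.60. Guaranteeing 80% per outcome at alpha 0.025 would need about 180 participants instead of 150.

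Under either rule, the same paragraph should say which contrast from the mixed model carries the test for each outcome. The 1-year contrast is one possibility.
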